#### 2.5.1. TY Leader Role

The TY leader role is responsible for planning, promoting and implementing the SLASF initiatives and events throughout the school year. Based on self-efficacy theory [29], TY leaders are a closer connection to the students in the schools than teachers, thus strengthen vicarious experiences. Moreover, social support and leadership from the TYs can reinforce the basic premise of proactive behaviour change [43]. The SLASF team can be identified by being given pins to wear on their uniform. Moreover, part of the time spent on SLASF activities can be used as part of a time bank for other volunteering programmes, such as, Gaisce the President’s Award. The selected SLASF youth leaders will receive their own distinct pins to wear on the uniform. 

#### 2.5.2. Activities for Certification

For schools to be successful in achieving the activities needed for certification, there is a yearly planner with guideline dates for task completion that the schools will use to keep on track. This also includes the accreditation visit. For example, the SLASF slideshows for the staff, team and youth leaders need to have been completed before the 2nd week of the school year. A designated training day takes place a week later. The purpose of this training day is to introduce the pilot schools to each other and the research team. The research team describes the whole year process evaluation and measurements taken throughout the year. There are co-design opportunities between the TY leaders and researchers to formulate the surveys used to collect data. The training day is not expected to run every year once feasibility is over. At this training day, two members of staff, the SLASF coordinator and another on the SLASF team take four student leaders to a training venue to learn about how to run the activities throughout the year. The website should also go live at the outset of the process. The website should encompass an easy to find link to the SLASF section of the site and there are the four core parts of the SLASF process; Physical Education; PA; Partnerships; and Active School Week.
Another activity that the school needs to complete is the SLASF Awareness Week. This should be completed two weeks after the training day. School census questionnaire is deployed a week after the awareness week and this precedes the official launch of the SLASF process.During the launch, there would be a school wide tug of war (TOW) competition that is planned, promoted and organised by the SLASF committee. For the launch day the overall winning TOW team will compete against a staff team at a whole school event to launch the SLASF initiative.

A school census questionnaire was developed to help the SLASF team to identify their action plan. Core questions about PA opportunities, physical education, involvement in extra-curriculum activities and barriers to PA were included in an online survey. For a week after the awareness week, the survey is available for completion. All responses are anonymous and completed confidentially. Class teachers supervise and help answer any technical questions related to the completion of the survey. The data is stored on a secure server that is only accessible to the researchers. However, the overall results for each variable would be computed and provided for the school to carry out their own descriptive analyses with the TY group. The TY class can then produce meaningful findings from the survey to show the school through the notice board and used for one of the planned actions. 

For the TOW event a free rope and a 2 ½ h workshop will be provided for each school. This will enable TYs to coach and officiate TOW competitions and SLASF committee members that complete the course will receive a TOW Community Coach certificate upon completion. Each class in the school will be involved in this event with each having 3 TOW teams that compete against each other during tutor time or physical education class to decide what team will represent the class. Each class TOW team competes against the other classes in their year group during lunchtime to find the best TOW team for their year. Local role models can be invited to help launch the event by taking part in one of the TOW teams. This event should take place before the mid-autumn break. 

After the mid-autumn break, the schools would have access to their school’s results from the school questionnaire. The SLASF teams are given a month to review the results and start to design an SLASF action plan. At least three action points need to be agreed upon by the SLASF team. The proposed SLASF actions should be presented to the Principal for agreement. The agreed actions are then implemented in the second half of the school year. Towards the end of the year, the three agreed actions will be reviewed by the SLASF team members and presented to the school Principal during the last two weeks of the school year.

In addition, all students in the selected year group in the school will take part in a four weeks PA module delivered by the Social and Personal Health Education (SPHE) teachers. There would have to be a ‘Did You Know?’ campaign around the school that helps raise awareness about the benefits of PA for teenagers, in particular the positive impact that PA has upon focus, concentration and academic achievement. Another practical task for the SLASF team is to signpost an Active School WALKWAY. The walkway is a route that can be used by the students in the school during recess time or under teacher supervision for active learning activities, before/after tests or during free classes. SLASF, in partnership with Get Ireland Walking, designed Active School WALKWAY packs consisting of colourful outdoor all-weather sign post plaques which include orienteering symbols. One of the tasks that the SLASF TY class have to undertake is to map, measure and erect the walkway signposts to create a school walking route. A school WALKWAY Day where all classes get the opportunity to complete the walkway route with their teachers on a nominated school day needs to be agreed by school management. Then it is organised and promoted by the SLASF TY team. The organised walkway can be used as part of orienteering activities during timetabled physical education, as well as other school-based initiatives. 

As the year ends, the school prepares for the accreditation visit for the certificate. A follow up visit takes place during the acquisition of the flag year. Prior to this, the school needs to organise a community mapping exercise and community events which should help with the design of the Active School Week (ASW) programme. The main aims of the ASW are to promote PA in a fun and inclusive way, as well as raising awareness about the availability and variety of PA opportunities for teenagers and their families in their local community. Throughout this week the school provides many and varied opportunities for staff and students to become more physically active throughout the school day.

#### 2.5.3. Expected Outcomes Tables and Measures

According to their training resources, the programme aims to impact on a number of areas. However, to measure them all, multiple sources are required. A collection of survey instruments can be used to measure some of the outcomes, whereas some interviews can be used to evaluate other outcomes. In addition, the programme is year-long and a whole-school approach, hence site visits and checking on progress through logbook entries would be used to determine the processes carried out during the study. In Table 2, there is a list of the areas that SLASF aims to promote and some measures that can be used to test these outcomes.

#### 2.5.4. Questionnaires

There are two types of online surveys carried out throughout the year. The basic survey is completed by the entire school. This survey is anonymous and the focus is on PA participation and barriers to school related physical activities. This survey is a compulsory part of the SLASF process. Administration of the survey is decided by the school, with the intention to cover the entire school. Ideally, a census sweep of the school takes place at the same time. However, there may be some technical issues that may prevent this from happening. For example, schools may have a limited number of computers accessing the internet at any one time (bandwidth limits), may have a limited number of units to complete the survey (lack of tablets or computers) or could not get all the school to take part at the same time (timetabling issues). The results of the survey will be given back to the school for the purpose to plan specific school-based interventions. Therefore, it is important that the mode of data collection, analysis and reporting can be completed quickly and easily. Failing all technical capabilities to collect from an online platform, extra resources would be dedicated to ensure double coding from pen and paper surveys. 

The second type of survey is a comprehensive survey, used for evaluating the feasibility of the study. The participants in this study input their user-ID so that the data can be linked from the beginning and end of the year long programme. Completion of the online survey takes place as one of the testing stations during the data collection visits. All the students have tablets or allocated to a school computer to complete the online survey. Details of the instruments are reported in Table 3.

### 2.6. Process Evaluation

#### 2.6.1. Logbook Activities

Each school is given a logbook to record their activities. This is used as part of the accreditation process and is used by the researchers to evaluate the processes that the school used. The logbook is mainly used by the SLASF team and the SLASF committees. Every week, the TY students have the opportunity to complete a small section in the diary to record what took place. The diary is linked to the school year and the expected timescale for carrying out specific activities. There is also a chart for the SLASF team to complete by recording the agreed actions to be carried out by the SLASF team. The team need to record the date of the agreed action, a short title for the action, the person(s) responsible, date of the action completed and a check box. 

The TY team carries out a brief version of the System of Observing Play and Leisure Activity in Youth (SOPLAY) [52]. SOPLAY is a direct observation tool that is used by the TYs to assess PA levels within specific PA areas in the school. Due to resources, the full SOPLAY protocol had to be reduced down to three specific areas around the school. Furthermore, the TYs use tablets to video record the specific area and retrospectively carry out the observations. It is designed in this way because the technology is more readily available in schools than the time when SOPLAY was created by McKenzie and colleagues [52]. Through, observing the video recordings, the results can be verified so the validity of the results are stronger. Trained researchers with the SOPLAY counting system can verify the results from the TYs by matching the observation results. The videos can also be used as part of a TY class, where the students can get an understanding of ways to record the different intensities of PA. The SOPLAY exercise is carried out over six times throughout the school year. The assignment of the dates are researcher assigned days. The TYs are informed of the audit in the morning of the day the recording takes place. To reduce potential bias in the results, the TYs are reminded not to tell others that they are carrying out the observation. Observations take place twice during lunchtimes, one 10 min into the beginning and the second when there is 10 minu left. 

Another activity recorded in the logbook is the SLASF committee meetings. The logbook provides space for six meetings throughout the year. The meeting minutes include the people in attendance, the areas of discussion and the actions that were agreed. There is also space in the logbook has space for a list of agreed action created by the TY class during their timetabled class time. To encourage compliance, there is room for information such as the agreed action, the person responsible and the date for completion. In addition, there is room in the logbook for the TY team and coordinator to note activities that take place in a specific week. For each week, tasks that are suggested, such as the slide show, presentation of the action plan and so forth are available for the TY and coordinator to help remind to be on track. 

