**Figure 2 jfmk-04-00016-f002:**
[figure not shown]
Actors of the Second Level Active school Flag.

**Table 1 jfmk-04-00016-t001:** Areas of focus for feasibility studies with measures and stopping criteria.

Focus	Measures	Stopping Criteria
Acceptability	Pragmatic survey instrument on suitability, satisfying and attractiveness for SLASF in schools for the TY and the whole-school at the end of the year.	When less than half the school students and TY consider SLASF to be suitable, satisfying or attractive to them.
	Focus group and interviews to describe the process of satisfaction of the programme, fit into the school’s culture and the positive and negative effect on the school.	When interviews describe strong statements that have a negative impact on the school’s culture or too much dissatisfaction to the programme.
Demand	PA audit of sections of the school.	No improvement over the academic year.
	Attendance list at the specific activities	Unsustainable numbers in attendance.
	Survey instrument based on readiness for PA behaviours.	Over half of students increased their readiness if they can.
	Focus groups based on the TY engagement in the SLASF process.	Discussions confirm low attendance rates and lack of demand for activities.
Implementation	Action Logs from the logbook.	Over half actions left incomplete
	Focus groups on implementation ease	Discussions where respondents report too many challenges preventing implementation
	Staff interviews	Data that suggests lack of resources to implement the programme and failures to execute the actions.
Practicality	Action plans for promotion of PA	If action plans could not be drawn up by the specified time frame
Adaptation	Registrations at events carried out as part of the action plan	Substantial decrease in participation over a 6 week period
Integration	Pre- and post-test results on PA opportunities and its participation	No increased opportunities since the beginning of the programme.
	Interviews with management about costs to organization and school policies	Descriptions whereby the costs are not sustainable. Indicators that there is a lack of staff
Expansion	Interviews of management	Descriptions of the uniqueness of the programme to the school and difficulties to roll out to other schools.
Limited Efficacy	Pre- and post-test results from the comprehensive surveys	Reduction in main outcome variables over the course of the year that is greater than the difference between each year cohort at the baseline measurements

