	ASF logbook entries	Notes that report barriers to completing actions that are not manageable
	PA audit	Low level of usage when compared with the beginning of the year

**Table 2 jfmk-04-00016-t002:** Aligning outcomes with measures.

SLASF Target Areas	Measures of Efficacy	Details
Physically educated	Self-efficacy in PA	Student survey
Physically active school community	Comprehensive Survey and focus groups	Survey item and discussions
Broad physical education	Whole-school survey and focus groups	List of physical education activities and discussions
Balanced physical education	Teacher scheme of work	Teacher records
More inclusiveness	Teacher scheme of work	Teacher records
Partnership with others to promote pa culture	TY logbook	Taster session from ASW
Active school week	TY logbook	Record of entries
Increased concentration	Harter scale	Student survey
Improved learning	Teachers perceptions	Student and teacher survey
Maintenance of discipline	Teacher records	Discipline records
Improved test results	Winter and summer test	Academic records
School enjoyment	Questionnaire	Student survey
Increase Daily PA	Accelerometers	Comprehensive Data
Reduced sitting time	Accelerometers	Comprehensive Data
Reduction in overweight and obesity	Self-report and anthropometric measures of height and weight	Comprehensive data

**Table 3 jfmk-04-00016-t003:** Battery of questionnaires.

Battery	Items	Response Scales	Psychometric Information
PA Screening measure	2 items on number of days in a week of at least 60 min of MVPA per day	0–7 days	Validity & Reliability [5,44]
PA opportunities	Modified items about local opportunities for PA to the context of schools instead of ‘residential area’	5 point scale, 1 = disagree a lot, 5 = agree a lot	Original items used from an interview guide.
The exercise self-efficacy scale for adolescents	10 items on confidence to participate in a variety of conditions	11 point sliding scale, 0 = not at all confident, 10 = very confident	Nigg & Courneya, 1999 [45]
PA peer support scale	4 items on the frequency of peers influence for PA	0 = never, 5 = every day	Prochaska et al., 2002 [46]
PA, plans, expectancy and intention	Modified 3 items on the planning, expectancy and intention to do PA in the coming week	1 = unlikely, 8 = likely	Hagger et al., 2001 [47]
Readiness for behaviour change	Single item to determine which stage of the transtheoretical model in terms of PA	Select one item of each stage of the transtheoretical model	Lee et al., 2001 [48]

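### The PA audit behind two Table 1 stopping rows is filmed and scored, unmasked, by the students who deliver the programme; researcher verification is only permissive

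*Protocol article*

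**What the plan says.** Protocol article, 2.6.1 (Logbook Activities), describes the audit as a shortened SOPLAY exercise covering three areas of the school. "SOPLAY is a direct observation tool that is used by the TYs to assess PA levels within specific PA areas in the school". The TY team films the areas on tablets and counts from the film afterwards. There are two observations per audit day, both at lunchtime.

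The same section contains several protections:
- On dates: "The assignment of the dates are researcher assigned days".
- On notice: "The TYs are informed of the audit in the morning of the day the recording takes place".
- The TYs are reminded not to tell others, expressly to reduce bias.
- On checking: "Trained researchers with the SOPLAY counting system can verify the results from the TYs by matching the observation results".

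Section 2.5.1 says of the same students: "The TY leader role is responsible for planning, promoting and implementing the SLASF initiatives and events throughout the school year".

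Table 1 uses the audit twice. Under Demand the stopping criterion is "No improvement over the academic year". Under Limited Efficacy it is "Low level of usage when compared with the beginning of the year". Section 2.8.3 plans descriptive statistics over time for the audit, read together with the logbook of actions.

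On events, 2.5.2 places tug-of-war rounds at lunchtime ("Each class TOW team competes against the other classes in their year group during lunchtime to find the best TOW team for their year"), before the mid-autumn break. It also describes a WALKWAY day for all classes and, with the year-end activities, an Active School Week with extra activity throughout the school day.

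**The concern.** The people whose programme is being judged produce the count that judges it. Having filmed the clips, they can be expected to know where in the year each belongs, and the article describes no masking of the scoring. Two things could then move the counts without any change in activity. One is expectation: hoping to see more activity late in the year. The other is drift: 2.6.1 notes that the videos may also be used to teach TY students how to record intensities, so their scoring may change with practice.

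Both audit criteria are comparisons across the year, so a bias that differs between early and late clips goes straight into them. Section 2.2.1 recruits the control schools for the survey component only, so the audit has no comparator in which scorer drift would show. Section 2.5 (in its list of certificate tasks) counts the space audits among the 17 tasks, and 2.6.1 makes the logbook part of accreditation. The scorers therefore belong to the team working towards the award.

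At stake are two inputs to the recommendation to stop, revise or go on to a randomised trial (section 3). Section 1.3 itself says the rules are predefined to prevent bias.

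**Working it through.** The plan states no sample size, SD or expected change for the audit, so there is no figure to reproduce. The check traces the roles, asks what each safeguard covers, and then counts.

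**1. Roles.** Delivery: TY students (2.5, 2.5.1). Filming: TY students (2.6.1). Primary scoring: TY students (2.6.1). Checking: trained researchers, permissively (2.6.1). Use: two rows of Table 1. The article does not say which count enters those rows when the two disagree.

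**2. What each safeguard covers.**

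| Safeguard in 2.6.1 | Advance staging | Scoring bias or drift | Choice of what is filmed | Real event-day activity |
|---|---|---|---|---|
| Researcher-set dates | limits | no | no | only if dates avoid events |
| Same-morning notice | limits | no | no | no |
| Reminder not to tell others | limits | no | no | no |
| Scoring from video | no | makes checking possible | no | no |
| Researchers may verify | no | only if done and given precedence | no | no |

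Scoring bias is the gap that stored video could close and that the text leaves open.

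**3. Volume.** Inputs from 2.6.1: three areas, two observations per audit day, and six audits. The wording on the number of audits could also mean more than six. Assume one clip per area per observation.
- Per school and audit day: 3 × 2 = 6 clips.
- All audits, three schools: 3 × 6 × 3 × 2 = 108 clips.
- First and last audits only: 3 × 2 × 3 × 2 = 36 clips.

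**4. Illustration of sensitivity.** Suppose true usage is unchanged, daily audit values are independent and normal with equal SD, and one audit day is shifted upwards by d between-day SDs. The value of d is assumed, because the document gives no SD. Φ is the normal distribution function. The chance of an apparent rise when the last audit is shifted is:
- first versus last: Φ(d/√2);
- linear slope over six equally spaced audits: Φ((2.5d/17.5) × √17.5) = Φ(0.598d);
- last three versus first three: Φ((d/3)/√(2/3)) = Φ(0.408d).

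| d | First vs last | Slope | Last three vs first three | First vs last, shift on the first audit |
|---|---|---|---|---|
| 0 | 0.50 | 0.50 | 0.50 | 0.50 |
| 0.5 | 0.64 | 0.62 | 0.58 | 0.36 |
| 1 | 0.76 | 0.73 | 0.66 | 0.24 |
| 2 | 0.92 | 0.88 | 0.79 | 0.08 |

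The final column is 1 − Φ(d/√2). The first-versus-last formula serves equally for a net scoring shift of d between the two audits. An upward shift late in the year pushes towards continuing; the same shift at the start pushes towards stopping. Using all six audits dampens the effect of one shifted day but does not remove it.

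**The case against.** The strongest reply is that 2.6.1 already addresses bias. Researchers choose the dates, the TYs learn of them only that morning, the counts come from film, and trained researchers can match them. The article also uses the word can loosely for work it evidently plans, so verification may be intended as routine. The share of clips checked and the agreement required are details that a full protocol may hold.

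Much of this stands. A reader might infer that the reminder not to tell others is the only safeguard; the section shows otherwise. A reader might also infer that same-morning notice lets the TYs stage activity. Short notice of a date set by someone else limits staging, so it counts in the plan's favour.

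A reader might further infer that audits will fall on event days. The article gives no audit date, and nothing places the tug-of-war or Active School Week in the three audited areas. The Figure 1 timeline was not available in the text reviewed and may bear on this. Overlap is only a possibility.

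Nor do the audit rows decide the outcome alone. They are two of 17, Demand also uses attendance, readiness and focus groups, and no text says that one row stops the programme.

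What the reply does not answer is the choice of scorer. Even on a generous reading of the verification sentence, the programme's deliverers make the first count, no masking is described, and nothing gives the researchers' count precedence.

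**Conclusion.** The concern holds in a limited form. Two of the 17 stopping rows rest on counts made by the students who deliver the programme, with checking that is permissive and no statement of whose count prevails. Expectation or drift in that scoring can move the audit result.

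The size of the bias is not known from the document. An upward bias late in the year is a reasonable expectation, but a reader who took it as established would go beyond the text. The probabilities above show only how sensitive a simple comparison is to an assumed shift; they do not estimate what will happen.

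Event-day overlap is a secondary, hypothetical point and its direction depends on timing. Tug-of-war rounds could raise the early reference and favour stopping; Active School Week could raise a late value and favour continuing.

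The change is worth making because a less biased count is available from video already being recorded, by researchers already named as verifiers.

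**What to change.** - **Source of the count.** State that the two audit rows in Table 1 use the trained researchers' counts from the stored video. Code the clips in random order, masked to date as far as the footage allows. Do this at least for the first and last audits (about 36 clips if there are six audits), and preferably for all (108).
- **TY counts.** Keep them as a class exercise and report their agreement with the researchers' counts.
- **Dates.** When assigning audit days, avoid tug-of-war lunchtime rounds, WALKWAY day and Active School Week, or flag any audit that falls on one and show the result with and without it.

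The cost is some researcher coding time, plus the small procedure of masking and shuffling clips. No new recordings are needed, and the dates are already in the researchers' hands. Masking may be imperfect, because the season or newly erected walkway signposts may be visible. Researcher coding corrects scoring bias only. It does not correct the TYs' choice of what to film or real extra activity on an event day; choosing or flagging dates deals with the latter.
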